#### **6.3.1. Individuals' inclusion Criteria**

Subjects must meet all the following criteria to be eligible for inclusion in the study:

- Age  $\geq$  65 years old
- Having a contact telephone number
- Taking at least one PPI (POM or OTC) continuously for  $>8$  weeks - omeprazole, lansoprazol, esomeprazol, pantoprazol, rabeprazole, as per International Non-Proprietary Names (A02BC, Anatomical Therapeutic Chemical (ATC) classification).
- Registered at the selected FHUs as self-reported by patients:
  - In the intervention group - FHU Uarcos (Arcos de Valdevez) or Terra da Nóbrega (Ponte da Barca) and,
  - In the control arm - FHUs listed on table 3 from the identified control municipalities.

#### **6.3.2. Exclusion Criteria**

Individuals who do not give their informed consent, live in nursing homes or assisted-living facilities, are unable to communicate or speak in Portuguese, have any cognitive impairment, or any other condition that does not allow them to understand the study objectives or the questionnaire completion as perceived by the pharmacist, will be excluded from the study.

#### **6.4. Study Enrollment and Patient Recruitment Procedures**

During the recruitment study period, a pop-up window will be generated on participating pharmacies' software Sifarma® whenever a PPI is dispensed in the pharmacies (intervention and control), so that the pharmacist will be warned to systematically assess individual's enrollment eligibility criteria. Eligible individuals will be invited to participate in the study.

The patient can refuse to participate, and the pharmacist will be instructed to fill in the refusal form with basic sociodemographic information (e.g gender, age group) and motives for refusal (**Annex 3**). If accepts to participate, he/she will be required to sign an informed consent before any data collection or intervention procedure.

The research team will monitor the pharmacies (intervention and control) through regular phone calls, to maximize patient enrollment and reach the target sample size. During the recruitment period a feedback report containing major key performance indicators (e.g., number of recruited patients) will be provided to pharmacies.

#### **6.5. Intervention and control**

The intervention consists of a multidisciplinary collaborative care framework between intervention pharmacies and FHU to firstly deprescribe inappropriate PPI and secondly to identify and solve other related medicines-safety problems such as drug-drug interactions. The patient-centered multifaceted intervention package has several components.

Firstly, following in-person patient eligibility assessment, recruitment, acceptance and informed consent signature, the pharmacist will collect study information regarding the PPI medicine use and beliefs, through the application of a structured paper-based questionnaire (**Annex 4**). Pharmacist will then assess the potential inappropriate use of PPI, considering the patient self-reported clinical indication for it use and the Deprescription algorithm (**Annex 5**). Following pharmacist will inform the patient about the screening result (unknown, possible recommendation to maintain the PPI or, possible recommendation to withdraw based in patients' self-report) and that he/she will be contacted by the research team in the following 48-72h for additional data collection, and by the GP in 1 to 2-week to assess the medication. Furthermore, the pharmacist will deliver a direct-to-patient oral and written educational information, in the shape of a booklet (**Annex 6**), concerning the rational use of medicines, PPI correct indications and safe use, deprescribing benefits and possible withdraw symptoms.

Secondly, after patient recruitment, a therapeutic profile will be drawn up and analyzed by the research team to list all medications taken by the patient in a regular basis and identify medication duplications and relevant drug-drug interactions (DDIs) (**Annex 7**). The therapeutic profile will be drafted based in extracted data from the pharmacies software regarding the sales associated to the patients' tax information number (NIF) and confirmed by patient self-report, via a telephone interview with the research team. DDIs will be assessed using Sifarma® software. In this telephone interview, the research team will confirm the use of the listed medications (prescription-only-medicines (POMs) and OTC). Further data for study purposes (e.g PROMs) will also be collected in the telephone interview (**Annex 8**). The final therapeutic profile and related safety information will then be sent to the community pharmacist by email (with access key) to be shared with the patient GP for clinical assessment.

Thirdly, the pharmacist will gather all the information, the PPI deprescribing recommendation and the therapeutic profile with identified moderate and severe DDIs provided by the research team and share with the GP. A specific paper case report form "Passaporte do utente" (**Annex 9**) will be used to exchange information between both pharmacists and GP.

Fourth, The GP with the information provided by the pharmacist and that in his/her medical records, will assess the PPI use and other reported safety issues (DDIs). The patient will be contacted by the GP to discuss the PPI deprescribing pertinence and strategy and, solve other possible medication related problems. All patients will be contacted by the GP preferably by telephone. A face-to-face consultation can be scheduled if the GP considers relevant. Fifth, the PPI withdrawal decision and adopted strategy agreed with the patient will be communicated to the pharmacist using the paper case report. Sixth, after the GP report to pharmacist, of the PPI withdrawal decision, pharmacist will contact the patient by telephone at 2 and 4 weeks, to monitor possible symptoms relapses, answer questions and if applicable, define with the patient a control-symptoms strategy (non-pharmacological) pre-agreed with the GPs under the designed intervention. The 4-week telephone interview will occur only on patients with PPI dose reduction or withdrawal indication. At the end of the withdrawal follow-up

---

We intend, as part of the intervention, to be the pharmacist to collect all information regarding patients' medication profile. However due to the Covid-19 pandemic, the research team thought to reduce patient-community pharmacist face-to-face interaction time, and withdrawal from the pharmacist intervention package the task not directly related with the main PPIs' deprescribing and educational goals.

period, pharmacist will share the follow-up information with the GP using the established communication model. If any severe symptom is identified during this time span, pharmacists can send an urgent alert email to the FHU research coordinator. To assist the pharmacist through all intervention, a complete intervention log form, which include the telephone interview script (**Annex 10**), will be made available by the research team.

Patients can at any moment seek advice with community pharmacies and/or general practitioners. The overview of the multifaceted collaborative intervention package is depicted in Figure 2. intervention details are accessible on the C-SENIoR Intervention Flowchart (**Annex 11**).

[figure not shown]

**Figure 2** - Overview of the C-SENIoR multifaceted collaborative intervention package

The educational booklet was developed by the research team (pharmacists and general practitioners) for the study purpose. We performed a literature review of resources already tested in deprescribing interventions and available online (e.g., <https://deprescribing.org/>) and followed Fajardo et al recommendations (88) concerning readability of patient education materials for deprescribing interventions. The booklet is being tested with PPI elderly users, regarding its readability, dimension, key messages comprehension and images understanding.

This project will have the assistance of a clinical research associate (CRA) who will guarantee the information change flow foreseen between pharmacies and FHUs in the intervention arm.

Patients recruited from pharmacies assigned to the control group will receive usual care. For both groups, a baseline paper-based questionnaires will be delivered by the pharmacist (Annex 4), and three

telephone interviews, will be conducted by the research team at baseline, 3- and 6-month follow-up, respectively, to collect study data (see table 1).

### *Training*

Before initiation of the study, both control and intervention pharmacists will receive training regarding study procedures or study and intervention procedures, respectively.

Control group pharmacists will be provided a training session to explain the study procedures focused on the eligibility criteria, enrolment strategy and questionnaires application. The intervention group pharmacists will also receive specific training on physiopathology changes in the elderly, deprescribing risks and benefits, intervention, and study procedures. The training sessions will be provided by the research team (2 pharmacists - [name] and [name] both with an Educational Training for Trainers certificate and 1 general practitioner) and will be delivered in webinar format of a 2 to 4-hour session. The training is mandatory to participate in the project. All intervention (this part just for intervention arm) and study materials will be delivered to the pharmacies by express mail. The trainers will not receive any payment for the preparation and training sessions.

A training session will also be delivered to all general practitioners of the FHUs intervention arm, mostly focused on the study procedures (e.g., aim, population, intervention design, schedule, materials), and Portuguese PPI- clinical guidance. The training will be delivered by the FHU coordinator, the CEFAR research team contact person, in an FHU internal meeting.

The research staff will be available to answer questions and provide support as necessary, to all community pharmacists and general practitioners from the intervention arm enrolled in the study.

## **6.6. Participant timeline**

This trial will have an estimated minimum recruitment period of two months, followed by a follow-up period of 6 months per patient. However, the recruitment period length will be redefined after the first month of the recruitment period, if needed.

Recruitment is expected to start in October 2022 ( $\pm 4$  months). Study 6-month follow-up is expected to end in March 2023 ( $\pm 4$  months) (base case).

### **6.7. Study Follow-up**

Study follow-ups include 2 telephone calls, and electronic data extraction from the pharmacies dispense software at 3- and 6-months post recruitment. Telephone interviews are expected to last 10-15 minutes.

### **6.8. Outcomes**

The outcomes are measured at patient level. Patient's outcomes data will be collected at baseline and at study follow-up points (3 and 6 months). Follow-up data can be collected within 1 month after or before these exact time-point. At baseline, data collection is performed through a face-to-face interview conducted by the pharmacist (before the intervention take place in the intervention arm), by electronic extraction from the pharmacies dispense software and by telephone interview led by the research team after the patient recruitment. Follow-up study data collection is conducted by the research team through patients' telephone interview and electronic extractions from the pharmacies dispense software. Intervention related data will be collected alongside the study.

For process outcomes and economic evaluation analysis, data will be collected from the intervention log form (**Annex 10**), from the case report form "Passaporte do utente" (**Annex 9**) developed for the information exchange between pharmacists and GP, and from the CRA monitoring form (**Annex12**). These materials will be collected for study purposes in the end of the intervention period.

#### *Primary outcomes*

The primary outcome is successful deprescription – discontinuation or decreased dose of PPI, defined as a statistically significant reduction in medication burden between the intervention and control group between baseline and 3- and 6-months follow-up ascertained by pharmacy medicine sales associated to the patients' NIF and confirmed by patient self-report.

Based on Deprescribing meaning (31), discontinuation of a PPI will be defined as:

- the lack of reported consumption assessed at 3 and 6-month follow-up, as well as the absence of initiation of another medicine from the same class, or;

- the reported dose-reduction assessed at 3 and 6-month follow-up, as well as the absence of initiation of another medicine from the same class.

The discontinuation/dose reduction rate among participants in the intervention arm will be compared to the discontinuation/dose reduction rate among participants in the control arm. In this way we will be able to determine the absolute rate of discontinuation attributable to the intervention.

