##### **Primary objective**

To evaluate the effectiveness of a community pharmacist-general practitioner collaborative intervention on the discontinuation of inappropriate PPI by community dwelling elderly, compared with usual care, as measured by the cessation or reduction of targeted medication at 6 months follow-up. The acronym C-SENioR stands for “Collaborative depreScribing intervENTION of PPI on community dwelling eldeRly”.

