#### **6.10. Potential harms and patient safety**

Because of the pharmacological characteristics of the PPI there is a possibility that the discontinuation might lead to symptoms relapse (e.g., rebound hyperacidity) or complications (95). However, the potential for serious harm due to adverse drug withdrawal events (ADWEs) appears to be rare (96) and several drug class specific deprescribing interventions have found no difference in the rate of ADWEs between control and intervention groups (35). We expect a low probability of relapses or complications as only non-evidenced based medications will be withdrawn and the best evidence deprescribing guidelines will be followed (87). Additionally, patients will have the pharmacist and general practitioner support to help them to manage potential symptomatology with non-drug approaches, use of OTC medicines or, if necessary, to review the PPI dose, indication to use on-demand or full restart of the medication based on the best evidence. Any suspected adverse drug event (ADE) acknowledged will be reported to the study research team and to the National Pharmacovigilance System through "Portal RAM" from the National Authority of Medicines and Health Products, I.P (INFARMED) site.

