#### **6.11. Sample size**

Our principal hypothesis is that our intervention will reduce the use of inappropriate PPIs compared to usual care.

Our assumption is that the intervention will reach a rate of discontinuation similar with that achieved in previous studies reporting medication withdrawals in intervention with collaborative work between pharmacists and GP, compared to usual care (minimum absolute difference of 20%)(79,97). Alongside,

we will also assume that a small rate of discontinuation will be observed in the group without the intervention (control Group) as much as of 10%.

Therefore, our study will be conducted to detect a minimal 20% increase in the rate of discontinuation of inappropriate medication use caused by the intervention compared with the usual care. Assuming an alpha of 5%, 90% power and an allocation ratio of 1:1, we estimate that the minimum total sample size to detect differences between intervention and control group is 178 patients (89 patients per group).

Considering a 20% lost to follow-up, then a total of 222 patients (111 per group) recruited in the participating pharmacies will be needed in this study.

The sample size was calculated using the software G\*Power version 3.1.9.6.

**Exact** - Proportions: Inequality, two independent groups (Fisher's exact test)

**Options:** Exact distribution

**Analysis:** A priori: Compute required sample size

|                |                             |   |           |
|----------------|-----------------------------|---|-----------|
| Input:  | Tail(s)                     | = | Two       |
|                | Proportion p1               | = | 0.1       |
|                | Proportion p2               | = | 0.3       |
|                | $\alpha$ err prob           | = | 0.05      |
|                | Power (1- $\beta$ err prob) | = | 0.90      |
|                | Allocation ratio N2/N1      | = | 1         |
| Output: | Sample size group 1         | = | 89        |
|                | Sample size group 2         | = | 89        |
|                | Total sample size           | = | 178       |
|                | Actual power                | = | 0.9017447 |
|                | Actual $\alpha$             | = | 0.0340267 |

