| PPI use indication (self-reported)                                                       | 
 
Do not know.
 
GERD with esophagitis or without esophagitis but with persistent symptoms
 
Peptic ulcer disease with recurrent episodes
 
Severe esophagitis
 
Zollinger-Ellison syndrome/ Barrett's esophagus
 
Peptic ulcer prevention in long-term NSAID users
 
GERD without esophagitis and symptoms
 
mild and moderate esophagitis
 
Dyspepsia without symptoms
 
Peptic ulcer disease without symptoms
 
Eradication for H. pylori bacteria
 
Other
 
 | Paper-based questionnaire                                                | T0         |
| PPI initial Prescriber                                                                   | 
 
General Practitioner
 
Gastroenterologist
 
Other. _____
 
Do not know
 
                                                                                                                                                                                                                                                                                                                                                                                                                                              | Paper-based questionnaire                                                | T0         |
| PPI continuous use                                                                       | 
 
Yes
 
No
 
                                                                                                                                                                                                                                                                                                                                                                                                                                                                                                                          | Pharmacy software confirmed by
telephone interview                    | T1, T2     |

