|                                                                                               |                                                                                                                                                                           |                     |         |
|-----------------------------------------------------------------------------------------------|---------------------------------------------------------------------------------------------------------------------------------------------------------------------------|---------------------|---------|
| Satisfaction with the overall GP intervention                                                 | 
 
• likert scale from 1 to 5 – not satisfied at all to very satisfied
 
                                                     | Telephone interview | T2      |
| Satisfaction with the global collaborative intervention                                       | 
 
• likert scale from 1 to 5 – not satisfied at all to very satisfied
 
                                                     | Telephone interview | T2      |
| General Practitioners /pharmacists intervention process (only in the intervention arm) |                                                                                                                                                                           |                     |         |
| Number GP appointments Intervention related                                                   | 
 
• n GP appointments
 
                                                                                                     | Telephone interview | T2      |
| Number GP appointments intervention related reported to pharmacists                           | 
 
• n GP appointments
 
                                                                                                     | Paper form          | ongoing |
| GP appointments date                                                                          | 
 
• dd/mm/yyyy
 
                                                                                                            | Paper form          | ongoing |

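### As planned, the primary comparison does not separate withdrawal of inappropriate PPI from withdrawal of PPI that the patient had reason to continue

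*Protocol*

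**What the plan says.** **Objective.** Section 4 sets out to evaluate the intervention's effect "on the discontinuation of inappropriate PPI by community dwelling elderly", measured by cessation or reduction at 6 months. Section 6.11 frames the 20-point effect as one on inappropriate medication use.

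**Eligibility.** Section 6.3.1 admits patients aged 65 or over who have taken any listed PPI continuously for more than 8 weeks. Appropriateness is not a criterion.

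**Endpoint.** Section 6.8 labels every stop or dose reduction, without initiation of another PPI, as successful deprescribing, and continues: "The discontinuation/dose reduction rate among participants in the intervention arm will be compared to the discontinuation/dose reduction rate among participants in the control arm". The primary model in section 6.15.2 and the cost-effectiveness outcome in section 6.17.4.1 use the same all-patient proportion. None requires that the PPI was inappropriate or that the GP advised withdrawal.

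**Appropriateness data.** Section 6.5 makes the pharmacist's screening a step of the intervention. Table 5 lists the screening result (deprescribe, maintain, inconclusive) and the GP decision under "General Practitioners /pharmacists intervention process (only in the intervention arm"). Table 5 also lists "PPI use indication (self-reported") at T0, taken from the paper questionnaire that section 6.5 gives to both groups.

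**Safety premise.** Section 6.10 expects few relapses because "only non-evidenced based medications will be withdrawn".

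**The concern.** The objective names one quantity and the endpoint measures a broader one. The protocol itself foresees patients with a reason to continue: maintaining the PPI is one of the screening results and one of the GP decisions, and the indication list includes conditions that section 3 cites as exceptions to avoiding long-term use. If such a patient stops, the stop adds to the estimated benefit exactly as a stop of an unnecessary PPI does. A less selective intervention could then show a larger risk difference, a smaller NNT and a lower cost per success.

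No planned outcome tests the premise in section 6.10. The process outcomes in section 6.8 count GP decisions and pharmacist-GP agreement, but none links the decision to what the patient then did.

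The non-randomised design adds to this. Control units were matched on type and PPI prescribing volume, not on indication, and the example confounders in section 7 do not include indication. The mix of patients with and without a reason to continue may therefore differ between arms.

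**Working it through.** **1. The plan's own figure.** Inputs from section 6.11: "Assuming an alpha of 5%, 90% power and an allocation ratio of 1:1"; "Proportions: Inequality, two independent groups (Fisher's exact test"), two-sided; control rate 0.10 ("a small rate of discontinuation will be observed in the group without the intervention (control Group) as much as of 10" per cent); intervention rate 0.30. Full enumeration of the exact power gives 0.8977 at 88 per group and 0.9017447 at 89. The stated 89 per group and stated power are reproduced. For 20% loss, 178/0.8 = 222.5 against the stated 222, an immaterial rounding. The sample-size arithmetic is sound. The question is which patients the 20 points refer to.

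**2. What the primary comparison estimates.** Let *f* be the share of enrolled patients whose PPI is inappropriate, assumed equal in both arms. Let d_I be the difference in stop-or-reduce rates among them, and d_K the difference among the rest. The planned all-patient difference is

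D = f × d_I + (1 − f) × d_K.

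The plan estimates D. The objective concerns d_I. Section 3 cites 25% to 80% inappropriate prescribing, so I use f = 0.25, 0.50 and 0.80 to show a range; the value in this cohort is not given.

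**3. Two assumed extremes.** These show what D leaves open and are not forecasts. Control rates are 0.10 in both groups throughout.

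- *Effect confined to inappropriate use* (d_I = 0.20, d_K = 0). D = 0.20 × f.
  - f = 0.25: D = 0.05; Fisher power at 89 per group 12.5%
  - f = 0.50: D = 0.10; power 39%
  - f = 0.80: D = 0.16; power 75%
- *Effect confined to the rest* (d_I = 0), with D = 0.20 as planned. The rate needed among the rest in the intervention arm is 0.10 + 0.20/(1 − f).
  - f = 0.25: 0.367
  - f = 0.50: 0.50
  - f = 0.80: 1.10, which is impossible. The most the rest can contribute is 0.20 × (1 − 0.10) = 0.18, so at least 2 of the 20 points would come from inappropriate use.

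At f = 0.25 or 0.50, an observed 0.30 versus 0.10 is thus arithmetically compatible with no effect on inappropriate use. D alone does not tell these cases apart.

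**4. Whether existing data could.** Section 6.5 bases the screening on the self-reported indication and the Annex 5 algorithm. The indication is recorded at T0 in both arms, so one rule could be applied to all patients. The answers include not knowing the indication and an open category, so some patients would be unclassifiable. The GP's reading of the record remains available in one arm only.

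**5. Precision within the class of interest.** Of 89 analysed per group, 89 × f gives about 22, 44 or 71 patients. At 0.10 versus 0.30, exact power is about 28%, 56% or 82%.

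**The case against.** The strongest reply is that the objective states its own measure, cessation or reduction of the targeted medication, and that an all-comer effect is a legitimate choice in a pragmatic trial. Use beyond 8 weeks also matches the threshold in the criteria cited in section 3. That stands, and it is why the all-comer analysis should remain primary. But those criteria carry exceptions that eligibility does not apply, so the threshold does not make all enrolled use inappropriate.

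A second reply is that section 6.15.1 foresees results by other subgroups, and that subgroup choice is normally left to the SAP. The only example given there is age group. What the protocol itself fixes is the endpoint definition and the recording of appropriateness in one arm, and this is where the mismatch with the objective lies.

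A reader might go further and infer three things that the documents do not support:

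- *That the trial is unable to make the separation.* The T0 indication exists in both arms, so a crude but comparable split is possible. It is simply not planned.
- *That every stop or reduction in a patient with an indication is a harm that the trial conceals.* Section 3 favours the lowest effective dose, so a reduction is not shown to be unwanted, and a stop may follow a GP's decision made with the medical record. The booklet also covers correct indications, and all intervention patients are to be contacted by the GP. Adverse drug events, gastric tests, emergency visits, hospital stays and EQ-5D-5L are collected without restriction by arm. In the intervention arm, the recorded decisions allow stops against advice to be identified.
- *That a definite part of the 20 points is spurious.* Any such figure needs stopping rates by appropriateness, and the protocol gives none.

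**Conclusion.** The point holds as a statement about the plan as written. The objective and the sample-size effect concern inappropriate PPI; eligibility, endpoint, model and economic outcome do not distinguish it; and the formal appropriateness assessments exist in one arm. A positive result would show that the intervention lowers PPI use. It would not by itself show that it lowers inappropriate use.

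The size is unknown. The figures above rest on assumed class effects, on equal class shares in the two arms, and on a literature range that need not apply to patients aged 65 or over with more than 8 weeks of use. They show how much the planned comparison leaves undetermined, not a bias of a given size. They are not evidence that the stated sample size was miscalculated. The change is worth making because the stated objective depends on it and the input data are already being collected.

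**What to change.** Keep the all-comer risk difference at 6 months as the primary analysis, and add the following.

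1. The research team applies the Annex 5 algorithm to the T0 indication of every patient in both arms, by the same rule and without using follow-up data. Each patient is classed as deprescribe, maintain or inconclusive.
2. Report the primary risk difference by this class, and name the deprescribe class as the result that addresses the stated objective.
3. In the maintain class, report complete stops by arm, separately from dose reductions, as a descriptive safety comparison. In the intervention arm, show which stops followed a GP decision to withdraw, so that supervised withdrawals are not presented as harms.

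The cost is one derived variable and one stratified table, with no new data collection foreseen. Annex 5 is a stand-alone document not reproduced in the protocol, so the team should confirm that the T0 data supply all its inputs. Self-report will misclassify some patients and leave an inconclusive class. Precision within classes will be lower, as step 5 of the working shows, so class results should be presented as estimates with confidence intervals.
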